**11.2 Analysis plan**

The unit of analysis will be each pregnancy. For each pregnant woman a complete data set consists of the following:

| Variable | Type of data | Variable classification | | | | |
| --- | --- | --- | --- | --- | --- | --- |
| Confounder | Evidence of placental malaria | Outcome measure | | |
| Predictive value of diagnostic | Infant birth weight | Maternal Hb |
| RDT on peripheral blood taken during 2nd trimester | Binary (positive / negative) |  |  | X |  |  |
| Microscopy of peripheral blood taken during 2nd trimester | 1. Binary (positive / negative)  2. Count for positives |  |  | X |  |  |
| PCR on peripheral blood taken during 2nd trimester | Binary (positive / negative) |  | X |  |  |  |
| RDT on peripheral blood taken during 3rd trimester | Binary (positive / negative) |  |  | X |  |  |
| Microscopy of peripheral blood taken during 3rd trimester | 1. Binary (positive / negative)  2. Count for positives |  |  | X |  |  |
| PCR peripheral blood taken during 3rd trimester | Binary (positive / negative) |  | X |  |  |  |
| RDT on peripheral blood taken during or shortly after delivery | Binary (positive / negative) |  |  | X |  |  |
| Microscopy of peripheral blood taken during or shortly after delivery | 1. Binary (positive / negative)  2. Count for positives |  |  | X |  |  |
| PCR result on peripheral blood taken during or shortly after delivery | Binary (positive / negative) |  | X |  |  |  |
| Placental histology for evidence of infection | Binary (positive / negative) |  | X |  |  |  |
| Diagnostic results of any additional visits to clinic (eg symptomatic infection) | Binary (positive / negative) |  | X |  |  |  |
| Maternal Hb at delivery | Continuous |  |  |  |  | X |
| Infant birth weight at delivery | Continuous |  |  |  | X |  |
| Study site | Nominal | X |  |  |  |  |
| Age | Continuous | X |  |  |  |  |
| Gravidity | Ordinal | X |  |  |  |  |
| SP treatment | Binary (yes/no) | X |  |  |  |  |
| Iron & folate supplementation | Binary (yes/no) | X |  |  |  |  |
| Bed net use | Binary (yes/no) | X |  |  |  |  |

The following definitions will be used:

- Evidence of placental malaria: a positive PCR result is obtained for any peripheral blood sample and / or there is evidence of placental infection by histology
- RDT positive: a positive RDT result is obtained from one or more blood samples
- Microscopy positive: parasites are detected by microscopy (thick film) in one or more of the blood samples

The accuracy of RDTs and peripheral microscopy at detecting placental malaria will be assessed by considering the sensitivity, specificity, positive predictive value and negative predictive value of each diagnostic compared to evidence of placental malaria. This analysis will be conducted for all samples combined and also separately for each study location. Marginal generalized linear models will be developed to assess the impact of confounders on predictive values.

The impact of RDT screening and treatment compared to standard IPT on infant birth weight and maternal Hb will be assessed for non-inferiority by testing the hypotheses:

1. Mean birth weight of infants whose mothers were RDT positive & treated with ACT/quinine ≥ mean birth weight of infants whose mothers were RDT negative (and received SP)
2. Mean Hb of mothers who were RDT positive & treated with ACT/quinine ≥ mean Hb of mothers who were RDT negative (and received SP)

Standard statistical techniques such as t-tests, ANOVA and regression modeling will be used to test these hypotheses and investigate the potential impact of confounders on birth weight and maternal Hb.

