Any symptoms reported by the participant at the visit will be investigated and managed according to the local standard of care by the health center staff clinician providing care, as described in section 7.3.4. Data will be collected on symptoms reported and any treatments given, and information on provision and use of routine antenatal care will be recorded. If, in the judgment of the health center staff, a participant requires referral for medical reasons, this will be done according to usual health center procedures as in section 7.3.4.

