Each lot of RDTs will undergo lot testing according to WHO guidelines57 before and at the end of the study. RDT testing will take place in the laboratory of [name] at the Centers for Disease Control and Prevention (CDC), Atlanta, Georgia, USA. Prior to the start of the study activities at each site, the RDTs to be evaluated will be stored in their original packaging at room temperature in a central storage space. Stocks of RDTs, adequate to complete training and the study at each site, will be transported to each health center prior to the training and pilot period at each site. Manufacturers recommend that RDTs be stored between 4 and 40° C. Temperature and humidity of the storage areas will not be controlled, but will be monitored and recorded regularly to document storage conditions at each site.

*7.6.2.2 RDTs to be evaluated*

The following criteria will be considered in selecting the RDTs for this evaluation: high performance in WHO/FIND standardized product testing,27 ease of use, safety (minimal exposure to blood during test preparation), completeness of packaging, appropriate packaging for transport and storage in tropical environments (each test individually wrapped in foil with plastic liner), reasonable market price, and reliability of the supply of the RDTs.

*7.6.2.3 Preparation of RDTs*

RDTs will be performed on maternal blood obtained by venipuncture at the time of each routine antenatal visit, and at the time of delivery. In addition, RDTs will be performed on placental blood obtained at delivery. Individual RDTs will be labeled with the participant’s unique study number and initials. A member of the study staff will prepare the RDTs according to manufacturer instructions. All personnel will use universal precautions when handling blood samples.

*7.6.2.4 Interpretation and recording of RDT results*

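### Section 11.2 defines evidence of placental malaria in two incompatible ways: the variable table includes additional-visit results, the written definition does not

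*Protocol*

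**What the plan says.** The variable table in Protocol section 11.2 assigns each variable to one of five columns: confounder, evidence of placental malaria, predictive value of the diagnostic, infant birth weight, or maternal Hb. The row "Diagnostic results of any additional visits to clinic (eg symptomatic infection") is a binary variable marked under evidence of placental malaria. The only other rows marked there are the three peripheral PCR results and placental histology. All RDT and microscopy rows (second trimester, third trimester, delivery) are marked under predictive value of the diagnostic.

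Below the table, the same section defines evidence of placental malaria as: "a positive PCR result is obtained for any peripheral blood sample and / or there is evidence of placental infection by histology". Additional-visit results do not appear there.

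The index results are defined without reference to scheduled samples. RDT positive means that "a positive RDT result is obtained from one or more blood samples"; microscopy positive means that "parasites are detected by microscopy (thick film) in one or more of the blood samples". Section 11.2 then derives sensitivity, specificity, PPV and NPV for "each diagnostic compared to evidence of placental malaria".

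The protocol does not name the test used at additional visits. For study RDTs, section 7.6.2.3 says: "RDTs will be performed on maternal blood obtained by venipuncture at the time of each routine antenatal visit, and at the time of delivery". Section 7.6.4 schedules peripheral PCR samples at the same times. Section 7.3.5 encourages women to come to the study site for care between visits and gives them a card to record care received elsewhere.

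**The concern.** Table and definition are both current text, and neither is said to override the other. They disagree about which women count as having placental malaria, the quantity against which every diagnostic is judged.

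The additional-visit test is probably an RDT or a blood smear. Section 3.1.2 describes PCR as unavailable outside research settings, study PCR samples are not scheduled at such visits, and histology is possible only after delivery. If the table is followed, a peripheral result from one of the methods under evaluation can make a woman reference-positive even when all her PCR results and her placental histology are negative.

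This affects NPV, the accuracy measure named as a primary outcome in section 11.1, and PPV, which appears in the second primary objective (section 4.1) and in the sample-size hypothesis (section 11.3). It also affects who is classed as having placental malaria in the other two primary outcomes of section 11.1, mean birth weight and mean maternal Hb.

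**Working it through.** **Is the column assignment an artefact of text extraction?** It does not look like one. The other rows fall where they should: site, age and gravidity in the first column, PCR and histology in the second, RDT and microscopy in the third, birth weight in the fourth, Hb in the fifth. The additional-visit row falls in the second.

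**Inputs.** Sensitivity 65% and specificity 98% are the planning values in section 11.3. The protocol gives neither the prevalence nor the frequency of positive sick visits, so both are assumptions. I take prevalence 20%, and let x be the share of all women who are negative on every PCR and on histology and whose only positive result is from an additional visit: x = 1%, 2.5% or 5%. The protocol states no accuracy figure for this point that could be reproduced.

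**Cells, as shares of all women, with additional-visit results excluded from index and reference**

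- TP = 0.65 × 0.20 = 0.130
- FN = 0.35 × 0.20 = 0.070
- FP = 0.02 × 0.80 = 0.016
- TN = 0.98 × 0.80 = 0.784

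PPV = 0.130/0.146 = 89.0%. NPV = 0.784/0.854 = 91.8%. Sensitivity = 65%.

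**Reading A: reference only.** This is the table taken on its own, since the row has no mark in the index column. The women in x move from TN to FN.

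- Sensitivity = 0.130/(0.200 + x) = 61.9%, 57.8%, 52.0%
- NPV = (0.784 − x)/0.854 = 90.6%, 88.9%, 85.9%
- PPV = 0.130/0.146 = 89.0%, unchanged

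**Reading B: reference and index.** The reference comes from the table and the index from the one-or-more-samples wording, with the test an RDT (or a smear, when microscopy is assessed). The women in x move from TN to TP.

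- PPV = (0.130 + x)/(0.146 + x) = 89.7%, 90.6%, 91.8%, a rise of 0.7, 1.6 and 2.8 points
- Sensitivity = (0.130 + x)/(0.200 + x) = 66.7%, 68.9%, 72.0%
- NPV = (0.784 − x)/(0.854 − x) = 91.7%, 91.6%, 91.3%

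**Reading C: index only.** The written definition sets the reference and the one-or-more-samples wording sets the index. The women in x move from TN to FP.

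- PPV = 0.130/(0.146 + x) = 83.3%, 76.0%, 66.3%
- Sensitivity stays at 65%, and NPV is as in reading B

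**Range over prevalence, at x = 5%, same formulas**

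| Prevalence | Excluded: PPV / NPV | A: sensitivity / NPV | B: PPV / sensitivity |
|---|---|---|---|
| 10% | 78.3% / 96.2% | 43.3% / 90.7% | 86.5% / 76.7% |
| 20% | 89.0% / 91.8% | 52.0% / 85.9% | 91.8% / 72.0% |
| 40% | 95.6% / 80.8% | 57.8% / 73.9% | 96.3% / 68.9% |

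In all readings the reference-positive share is either the assumed prevalence or, under A and B, the prevalence plus x: at 20% it becomes 21%, 22.5% or 25%. The latter groups would carry over to the birth weight and Hb comparisons.

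**The case against.** The best defence is that the written definition is introduced as the one to be used and excludes additional-visit results, so the table mark may be no more than a slip. That is plausible, but the section does not say so, and an analyst coding from the table would build a different reference.

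A second defence is that the affected group may be small. Any positive peripheral PCR already makes a woman reference-positive, and histology can show past infection. The row therefore matters only for women negative on both. This stands: x is unknown and could be below the values used here.

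A reader might infer that a sick-visit RDT becomes a true positive by construction. The documents do not establish that. It needs three things at once: the table must override the definition, the test must be an RDT, and its sample must count toward RDT positivity. The table itself lists index RDTs only for the two trimesters and delivery; read consistently, it makes the row reference only, and the error then runs the other way.

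A reader might also set reading B against reading C and conclude that PPV is inflated by 6 to 26 points (89.7 − 83.3 up to 91.8 − 66.3). Most of that gap comes from counting unscheduled RDTs as index results. Against a plan that uses them nowhere, the inflation under B at 20% prevalence is 0.7 to 2.8 points.

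Nor do the documents show that sick visits are tested by RDT or smear. The statement that symptoms "will be investigated and managed according to the local standard of care by the health center staff clinician" is in section 7.4.4 and concerns symptoms reported at a scheduled visit. A distorted comparison between sites is likewise inference: section 11.2 plans analyses by location but no formal contrast between them.

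**Conclusion.** The point holds as a contradiction within section 11.2 about the reference standard. Its effect has no single direction. If the table governs and the result enters the reference only, sensitivity and NPV are understated: at 20% prevalence, NPV falls by 1.2 to 5.9 points and sensitivity by 3 to 13 points. If it enters both index and reference, PPV and sensitivity are overstated, by 0.7 to 2.8 and by 2 to 7 points respectively, and NPV changes by at most 0.5 points. If the written definition governs, the reference is unaffected, and the open question is whether unscheduled samples count toward RDT or microscopy positivity.

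These sizes rest on the assumed prevalence and share of affected women, neither of which the protocol gives. The contradiction itself rests on no assumption. It is more than missing detail, because a stated rule, if followed, would bias at least one of the accuracy measures that the study is designed to estimate.

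**What to change.** In section 11.2, remove the additional-visit row from the evidence-of-placental-malaria column so that the table agrees with the written definition. Add one sentence stating that tests done at unscheduled visits count toward neither the index result (RDT or microscopy positive) nor the reference. Keep these results, with their dates, for the secondary objective on risk of symptomatic malaria (section 4.1).

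The cost is one table cell and one sentence, with no new data collection. Accuracy figures may shift slightly compared with an analysis coded from the present table.

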For purposes of epidemiological investigations, the gold standard for diagnosis of malaria in pregnancy is histopathological examination of the placenta after delivery.15-17 As recently summarized by Rogerson, et al, microscopic observation of histological changes in the placenta, including the presence of hemozoin deposits, may be used to confirm current and previous malaria infections, and a variety of laboratory protocols have been suggested for preparation of such samples.16, 18 A number of studies have documented the low sensitivity of light microscopy of peripheral blood smears for detecting placental infection.19 Importantly, some studies have indicated that submicroscopic malaria infections, identified with PCR or antigen-detection tests, may be associated with negative clinical outcomes including maternal anemia19, 20 and low birth weight.21 However, PCR is not available outside research settings, and antigen-detection tests have not yet been evaluated adequately for use in pregnancy.

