## 4.1 General objective

To determine whether screening pregnant women for malaria with RDTs may detect placental infection and predict risk of poor birth outcomes due to malaria in areas of varied malaria transmission in Africa.

Specific primary objectives:

1. To compare the results of RDTs, microscopy and PCR performed on peripheral blood from women in the second and third trimesters of pregnancy in malaria-endemic areas of Africa.
2. To determine the positive and negative predictive values of results of RDTs, microscopy and PCR performed on peripheral blood from women in the second and third trimesters of pregnancy, as compared with evidence of placental infection by histological examination after delivery.

Specific secondary objectives:

1. To measure and compare the frequency of pregnancy outcomes (infant birth weights, maternal hemoglobin), prevalence of placental malaria, and risk of symptomatic malaria among women in the study cohort. Participants who test positive by RDT at the time of usual IPTp administration will receive artemisinin-combination treatment (ACT) or quinine; participants who test negative by RDT will receive standard-of-care IPTp with SP.
2. To collect samples for future laboratory analyses related to malaria in pregnancy, including the measurement of the prevalence of molecular markers of antimalarial resistance in the study cohorts.
3. **STUDY DESIGN**

(See Figure 1 on next page.) Women will be enrolled at their initial presentation for antenatal care after quickening, i.e. on the first antenatal visit when they are eligible for IPTp according to WHO recommendations.2 On the usual IPTp schedule, typically once in the second and once in the third trimester, blood will be collected from all participants for RDT testing, preparation of thick and thin smears for light microscopy, and PCR. RDTs detecting histidine-rich protein 2 (HRP2) and plasmodium lactate dehydrogenase (pLDH) will be used for testing. All participants with negative RDT results will receive SP, and those with a positive RDT result will receive ACT or quinine (according to national policy for treatment of malaria in pregnancy). All participants will be followed up to delivery. At delivery maternal peripheral and placental blood samples will be collected for RDT testing, light microscopy, and PCR, and placental tissue samples will be processed for histopathological examination. Measurement of maternal hemoglobin and infant birth weight will be obtained.

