**11.1 Study outcome measures**

Results of peripheral blood tests performed during gestation will be analyzed for associations with evidence of placental malaria and pregnancy outcomes. The statistical analysis will focus on three primary outcomes: 1) negative predictive power of malaria RDTs, peripheral blood films and PCR performed on peripheral blood to diagnose placental malaria during gestation, 2) association of placental malaria during gestation on mean infant birth weight and 3) association of placental malaria during gestation on mean maternal Hb. These outcomes will be used to assess the potential utility of RDTs as screening tests to identify clinically significant malaria infections at a time when effective preventive measures may be taken. Other factors known to influence the study outcomes, including iron and folate supplementation, bed net use and administration of antihelminthic drugs will be treated as confounders in the analysis. In addition, stratified analysis will be conducted to assess these associations within subgroups based on geographic location, estimates of malaria endemicity, participant age, and parity (gravida class).

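### Section 11.2 lets any positive peripheral-blood PCR count as placental malaria, although primary objective 2 names placental histology as the reference and PCR as a test under evaluation

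*Protocol*

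**What the plan says.** The objectives and the analysis section of the protocol describe different reference standards.

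- **Objective (section 2, repeated in section 4.1).** Primary objective 2 is "To determine the positive and negative predictive values of results of RDTs, microscopy and PCR performed on peripheral blood", taken in the second and third trimesters, "as compared with evidence of placental infection by histological examination after delivery". PCR is one of three index tests and histology is the reference.
- **Background (section 3.1.2).** For epidemiological work, "the gold standard for diagnosis of malaria in pregnancy is histopathological examination of the placenta after delivery". The same paragraph says that histology can confirm both current and previous infection.
- **Outcome (section 11.1).** Primary outcome 1 is "negative predictive power of malaria RDTs, peripheral blood films and PCR performed on peripheral blood to diagnose placental malaria during gestation". Primary outcomes 2 and 3 are the associations of placental malaria with mean birth weight and mean maternal Hb.
- **Definition (section 11.2).** Evidence of placental malaria means that "a positive PCR result is obtained for any peripheral blood sample and / or there is evidence of placental infection by histology". The variable table agrees for PCR: the second-trimester, third-trimester and delivery PCR rows are all marked in the evidence-of-placental-malaria column, and none in the predictive-value column.
- **Table row (section 11.2).** The row beginning "Diagnostic results of any additional visits to clinic (eg symptomatic infection" is also marked in the evidence column, but the written definition does not include it.
- **Analysis (section 11.2).** "The accuracy of RDTs and peripheral microscopy at detecting placental malaria will be assessed" by sensitivity, specificity, PPV and NPV against evidence of placental malaria. PCR is not among the tests named.

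**The concern.** The study asks whether a blood test during pregnancy identifies placental infection. Under section 11.2, a woman with one positive peripheral PCR at any visit has placental malaria whatever her placenta shows. This has three consequences.

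1. PCR cannot be both an index test and sufficient for a positive reference, so the PCR part of objective 2 and outcome 1 is lost in one way or another.
2. RDT and microscopy are scored partly on agreement with a PCR done on blood from the same draw. That is close to primary objective 1, which already compares the three tests on peripheral blood.
3. The same variable is the exposure in primary outcomes 2 and 3 as section 11.1 words them, so the definition reaches all three primary outcomes.

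This is not a detail left for a SAP. The protocol fixes the reference standard, and fixes it against its own objective.

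**Working it through.** **1. What follows from the text alone (PCR).** Let H be histology positive, P be PCR positive at any visit, and C = H or P be the section 11.2 composite.

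- PPV of any-visit PCR against C: every P-positive woman is C-positive, so PPV = 100%.
- Specificity against C: every C-negative woman is P-negative, so specificity = 100%.
- NPV against C: among P-negative women C reduces to H, so the NPV is the same as against histology.
- NPV of PCR at a single visit: a woman negative at that visit but positive at another counts as a false negative even with a clean placenta, so this NPV can only stay equal or fall.

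Section 11.2 read literally assesses only RDT and microscopy. In that case none of these PCR figures is produced and that part of the objective goes unanswered.

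**2. Illustration for RDT.** The protocol gives no histology or PCR prevalence by site, so the rates are assumed: H 20%, P 30%, both 15%; RDT positive in 65% of P-positive and 1% of P-negative women, independently of H given P.

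| Cell | Share | RDT positive |
|---|---|---|
| H+ P+ | 0.15 | 0.15 × 0.65 = 0.0975 |
| H+ P− | 0.05 | 0.05 × 0.01 = 0.0005 |
| H− P+ | 0.15 | 0.15 × 0.65 = 0.0975 |
| H− P− | 0.65 | 0.65 × 0.01 = 0.0065 |
| Total | 1.00 | 0.2020 |

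| Quantity | Against histology | Against composite |
|---|---|---|
| Prevalence | 0.20 | 0.20 + 0.15 = 0.35 |
| RDT PPV | 0.0980 / 0.2020 = 0.49 | 0.1955 / 0.2020 = 0.97 |
| RDT NPV | (0.80 − 0.1040) / 0.7980 = 0.87 | (0.65 − 0.0065) / 0.7980 = 0.81 |
| Any-visit PCR PPV | 0.15 / 0.30 = 0.50 | 1.00 by construction |
| Any-visit PCR NPV | 0.65 / 0.70 = 0.93 | 0.65 / 0.70 = 0.93 |

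Of the composite-positive women, 0.15 / 0.35 = 43% have no histological infection.

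**3. Effect on the section 11.3 hypothesis.** The null there is that PPV is at most prevalence + α, or NPV at most 1 − prevalence, with α = 0.4 for Uganda and Burkina Faso.

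- Histology: PPV 0.49 against 0.20 + 0.40 = 0.60, not met.
- Composite: PPV 0.97 against 0.35 + 0.40 = 0.75, met.
- NPV exceeds its bar both ways (0.87 against 0.80; 0.81 against 0.65), so PPV decides.

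**4. Other assumed rates.** The grid crosses histology prevalence 10, 25 and 40%, PCR positive in 5, 15 and 30% of histology-negative women, and PCR positive in 70 or 85% of histology-positive women. RDT is positive in 65% of PCR-positive and 2% of PCR-negative women. Across these 18 combinations:

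- RDT PPV is 20–88% against histology and 82–98% against the composite.
- NPV is lower against the composite by about 1 to 12 points.
- Prevalence is higher by 3 to 27 points.
- Comparing expected PPV with prevalence + 0.4, the composite meets the bar and histology does not in 11 combinations (one only at the margin, 0.499 against 0.500). Both meet it in 5 and neither in 2.

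The combination with 25%, 15% and 85% gives PPV 0.62 against 0.65, then 0.94 against 0.76.

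**The case against.** **Section 11.2 is consistent with itself about PCR.** The table and definition use PCR as reference, and the accuracy sentence leaves it out of the tests. A reader might infer that the plan scores PCR against itself; section 11.2 does not say so. The 100% figures arise only if objective 2 and outcome 1 are run with the section 11.2 definition. This stands and limits the claim, but the alternative is that PCR is not evaluated at all.

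**The named primary measure is NPV.** The composite leaves any-visit PCR NPV unchanged and makes RDT NPV look worse. It is therefore wrong to say that the composite flatters the RDT throughout; the inflation is in PPV. PPV still matters, because it is in objective 2 and in the section 11.3 hypothesis.

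**There may be a reason for the composite.** Outcome 1 speaks of placental malaria during gestation, and RDT-positive women are treated before the placenta is examined. The protocol does not offer this rationale, and section 3.1.2 says that histology can also show past infection. The point supports a secondary analysis, not a silent change of reference.

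**The birth-weight effect cannot be quantified.** A reader might infer that about 123 g is diluted to 123 × 0.20 / 0.35 = 70 g, below the 85 g the study can detect. The documents do not support that, for three reasons:

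- Section 11.3 does not tie 123 g or 85 g to this contrast, and the hypotheses in section 11.2 compare RDT groups.
- Section 3.1.2 allows that submicroscopic infection may itself affect Hb and birth weight.
- If 85 g applied at 20% exposure, the detectable difference at 35% would be 85 × √(0.16 / 0.2275) ≈ 71 g, so nothing is left of the gap.

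**Conclusion.** The contradiction holds on the wording alone. Objective 2 names histology as reference and PCR as index test; section 11.2 makes any positive peripheral PCR sufficient for the reference and does not assess PCR. The PCR part of objective 2 and outcome 1 is unanalysed or, for PPV and specificity of any-visit PCR, predetermined.

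For RDT and microscopy the target is mixed, not replaced: every histology-positive woman remains reference-positive. It would go too far to say that the predictive values no longer concern placental infection.

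The size of the distortion rests on assumed prevalences and overlap, and on RDT being independent of histology given PCR. On those assumptions RDT PPV rises in every combination tried, NPV falls, and the PPV conclusion can reverse, though not always. The exposure in primary outcomes 2 and 3 is mixed in the same way, but no gram figure can be put on it. The additional-visits row is a smaller inconsistency between the table and the written definition.

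**What to change.** Reconcile sections 2, 4.1, 11.1 and 11.2:

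- Make placental histology the primary reference for objective 2 and the definition of the placental-malaria exposure in primary outcomes 2 and 3.
- Move the three peripheral PCR rows from the evidence column to the predictive-value column, and name PCR in the accuracy analysis.
- Remove the additional-visits row from the evidence column.
- Keep the composite, if wanted, as a labelled secondary reference (any malaria infection in pregnancy) for RDT and microscopy only.

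No new data are needed, since histology is already collected at delivery. The cost is more than wording. There will be fewer reference-positive women, and no reference result where the placenta is missing.

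The prevalence, 65% sensitivity and 98% specificity behind section 11.3 must also be rechecked for a histology reference, and the stated power restated. Section 11.3 does not say which reference those accuracy figures come from; section 3.1.2 reports a similar pair, 65% and 99%, for RDT against PCR on the same blood. In the illustration above, PPV against histology is below the + 0.4 bar, so the present hypothesis may not be attainable on that reference.
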